## 3. Planned Reporting of Results

The TIDieR checklist [42] will be followed in reporting the development of SPARKED, ensuring thorough reporting and replicability of the intervention. The report will include detailed descriptions of the intervention elements, such as materials, procedures, interventionists, mode of delivery, the number of SPARKED sessions, and any modifications implemented.

Triangulation in this research will involve the combination of key findings from co-design SSIs with participants who have MDD and their family members, surveys of mental health professionals, and focus group discussions with mental health professionals. This approach will enable an in-depth understanding of diverse perspectives on telehealth family psychoeducational intervention for MDD. Themes and codes derived from qualitative data will be systematically tabulated, while the contextual narratives will be presented.

Secondary outcomes of the feasibility study of SPARKED will be tabulated across different measurement timepoints. Results on recruitment, retention, and study completion rates will guide the timeline and study duration of a future RCT within the same context. Likewise, feedback on SPARKED (retrospective acceptability) will be used to improve the SPARKED protocol for a subsequent RCT.

## 4. Discussion

This protocol details the co-design strategies and feasibility assessment of SPARKED, a family psychoeducational intervention for MDD, delivered through telehealth. This study will also examine the preliminary effects of SPARKED on both clinically related outcomes (antidepressant adherence and depression severity) and non-clinically related outcomes (medication necessity beliefs and concerns, as well as personal recovery). The results on these outcomes will indicate the direction of an effect and will not be used to determine an effect size for a sample size calculation in a subsequent fully powered trial.

Major depressive disorder is a debilitating mental health condition that significantly impacts an individual’s life and, consequently, their family [65], thereby contributing to the burden of MDD. The impact of MDD is further compounded, given that residual depressive symptoms may persist even after remission [66] and potentially impair global functioning [67]. Even so, research indicates high rates of nonadherence to antidepressant treatment [68,69], despite evidence supporting its efficacy [70] and effectiveness [71] compared to placebos. A study conducted among patients from the United States and five European countries revealed that antidepressant nonadherence persisted longer due to a lack of belief in the necessity for the medication [72]. Thus, ensuring that individuals who opt for antidepressant treatment are adequately informed to make informed decisions regarding their treatment and feel empowered to discuss their choices with their healthcare providers is of paramount importance.

This protocol, however, recognises potential challenges associated with the use of telehealth for mental health in regional areas. A study conducted at a regional mental health service in Australia identified several limitations of videoconferencing, including a lack of devices, unreliable internet connectivity, technical issues, privacy concerns, and online fatigue [35]. These findings are consistent with evidence from a systematic review overview that identified infrastructure- and technical-related barriers, healthcare providers’ concerns regarding increased workload and privacy, and inadequate training on digital health technologies [73]. To ensure that dyadic participants involved in the feasibility study have access to phone credit or internet to participate in the sessions, 2 GB of data will be provided to them before each SPARKED session and follow-up session. Despite issues with telehealth use, mental health service users and providers see telehealth as a valuable way to improve access to mental health care, ensure regular reviews, and support patients who face engagement challenges due to low energy, anxiety, or depression [35]. Therefore, to successfully implement telehealth in mental health services, investment in telehealth infrastructure and structured staff training is necessary to overcome identified barriers.

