The proposed study, therefore, aims to co-design FPE, known as Supportive Program for Advancing Recovery, Knowledge, and Empowerment in Depression (SPARKED), and to assess the feasibility and acceptability of SPARKED delivered through telehealth among individuals with MDD and their families. The primary objectives of the study are as follows:To develop SPARKED through the involvement of patients, patients’ families, and mental health professionals.To determine the feasibility of SPARKED through assessing recruitment and retention rates.To determine the feasibility of outcome measure completion and return rates.To determine the acceptability of SPARKED at pre-intervention, during intervention delivery, and post-intervention.

The secondary objective of the study is to assess the preliminary effects of SPARKED on personal recovery, depression severity, antidepressant adherence, and necessity beliefs and concerns about antidepressants among individuals with MDD.

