### 2.3. Study Phase 2: Feasibility Study of SPARKED

#### 2.3.1. Study Design

A single-group, pre-post feasibility trial with an embedded qualitative evaluation.

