#### 2.3.3. Participants and Sample Size

Patient–family member dyads will be recruited through study flyers or a GP- or nurse practitioner-informed referral pathway.

Inclusion criteria are as follows: (i) an adult (aged 18 years or older) diagnosed with MDD who has been prescribed at least one antidepressant medication for treating the disorder and can provide a formal record of a current prescription, (ii) an adult with MDD who does not have any other serious mental or physical illness, (iii) an adult with MDD who has an adult family member, a carer, or significant other supporting themat home, and (iv) both the adult with MDD and their support person consent to participate in the study.

Exclusion criteria are: (i) an adult with MDD whose family member, carer or significant other cannot participate in the study, (ii) an adult family member of an adult with MDD who declines to participate, (iii) an adult with MDD identified with high suicide risk or current suicidal ideation using a suicide risk assessment tool [50], and (iv) an adult with MDD or a family member with a serious mental or physical health condition, cognitive impairment, or hearing impairment without a hearing aid. These health conditions may affect an individual’s ability to participate effectively in telehealth sessions.

The SS-PROGRESS WebApp (SS-PROGRESS) [51] was used to calculate the sample size required for the binary feasibility outcomes for estimation and hypothesis testing of pro-gression criteria. The 1-sample 1-tailed binomial exact test tests the null hypothesis that the true feasibility outcome is not greater than the upper “RED” stop limit [52]. Assuming an alpha of 0.05 and a beta of 0.2, we applied a minimum value of acceptable feasibility of 34% (indicating the smallest percentage for an outcome, which suggests that the main study would be feasible) and an expected value of 70% for each feasibility objective, resulting in a minimum sample size of 13.

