#### 2.3.9. Quality Assurance and Data Analysis

The study team will undertake quality assurance activities as previously outlined in Section 2.2.3. Data analysis will include both descriptive and inferential statistics.

Outcomes related to feasibility and acceptability (both prospective and concurrent) will be presented as either absolute or relative counts. Data collected through the SSIs (retrospective acceptability data) will undergo thematic analysis following the same procedure outlined in Study Phase 1. Codes and themes identified through this process will be used to refine the SPARKED guide and protocol for future large-scale trials. Conversely, data from each outcome measure will be prepared according to the developer’s instructions. Missing data will be handled using the pairwise deletion method, where missing data are omitted on an analysis-by-analysis basis. Given the small sample size, the Friedman test (significance level of 0.05) will be used to assess whether there are significant differences in the means of outcome measurements across the three measurement time points. The results of this analysis are entirely exploratory research findings.

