### 4.2. Limitations

This protocol has some limitations. The six-week post-intervention follow-up period is relatively short, as the study’s primary aim is to assess the feasibility of the intervention and data collection methods before conducting a larger trial with a longer follow-up. As such, the study will not adequately capture the long-term effects of SPARKED. Next, the feasibility study phase focuses on patient-related outcomes. Evaluating outcomes among family members could have offered an opportunity to ascertain whether SPARKED influences outcomes for both patients and their families. In addition, the small sample size will not permit the evaluation of the intervention’s effect size. Consequently, this study cannot draw strong conclusions regarding the effects of SPARKED. A large-scale RCT of SPARKED will be required to determine the effectiveness of the intervention. Next, the exclusion criteria regarding individuals who are assessed to have imminent suicidal risks limit the generalisability of SPARKED. To improve the generalisability of this research, future studies should consider implementing strategies to optimise contacts with participants for monitoring and assessing suicide risks, as well as establishing a pathway for escalated care. Finally, using telehealth to deliver SPARKED might inadvertently exclude people who lack access to digital devices or digital skills. While this research will report all technical challenges encountered during the study (context-related) to help tailor solutions for future research, future studies should consider providing an easy-to-understand graphic guide on how to use devices or offering in-person support for participants to address this limitation.

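### The secondary results are said to show the direction of SPARKED's effect, but a single group without a comparator can show only the direction of within-patient change

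*Protocol article*

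**What the plan says.** The Introduction of the protocol article sets as secondary objective to "assess the preliminary effects of SPARKED on personal recovery, depression severity, antidepressant adherence" and beliefs about antidepressants. Section 4 (Discussion) repeats the aim and adds: "The results on these outcomes will indicate the direction of an effect". The same sentence goes on to rule out using the results to size a later trial. Section 4.1 counts exploring the impact of the intervention on patient outcomes as a strength, and Section 4.3 speaks of its preliminary impact.

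Section 2.3.1 gives the design: "A single-group, pre-post feasibility trial with an embedded qualitative evaluation". Section 2.3.3 admits a patient who "has been prescribed at least one antidepressant medication for treating the disorder and can provide a formal record of a current prescription". Section 2.3.9 specifies that "the Friedman test (significance level of 0.05) will be used to assess whether there are significant differences in the means of outcome measurements" across baseline, Week 6 and Week 12.

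Section 4.2 says that "the small sample size will not permit the evaluation of the" effect size, concludes from this that strong conclusions about effects cannot be drawn, and calls for a large randomised trial. The lack of a control group and the concurrent drug treatment are not among the limitations listed.

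**The concern.** The direction of an effect of SPARKED is a causal quantity: it compares patients' scores with what they would have been without the programme. A single group observed before and after gives no estimate of that second term. The article therefore claims a property that its design does not have, and then gives sample size as the reason for caution.

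What is at stake is the sentence that the results paper may write about the PHQ-9, RAS-DS, MARS-5 and BMQ-Specific scores. Under the present wording, a shift in the group's scores could be reported as showing which way SPARKED works. A reader of Section 4.2 could also conclude that recruiting more dyads to the same design would settle the matter.

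**Working it through.** **The plan's own figure.** The only sample size given is the minimum of 13 in Section 2.3.3. It comes from a one-sided exact binomial test at alpha 0.05 and power 80%, with rates of 34% and 70%. With n = 13 and success declared at 8 or more, the type I error is 0.039 at 34% and the power at 70% is 0.835. At n = 12 the power is 0.724. The figure of 13 reproduces, but it serves the feasibility rates and says nothing about the secondary outcomes.

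**What the secondary data can identify.** For each outcome:

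expected pre-post change = effect of SPARKED + background change.

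Background change covers natural course, response to or changes in other treatment, and repeated self-report. The design yields one equation with two unknowns. The sign of the left side fixes the sign of the first term only if background change is known to be zero, or known to be smaller in size than the observed change. The documents do not say either.

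**Illustration.** Let d be background change and e the SPARKED effect, both in SDs of the change score, with positive meaning favourable. Treating the mean change as approximately normal,

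P(mean change favourable) = Phi((d + e) x sqrt(n)).

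The documents give no value for d, so it is an assumption and is shown on both sides of zero. With n = 13, sqrt(n) = 3.606.

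| d | e | (d + e) x 3.606 | P(favourable) |
|---|---|---|---|
| -0.2 | 0 | -0.72 | 0.235 |
| 0 | 0 | 0 | 0.50 |
| +0.2 | 0 | 0.72 | 0.765 |
| +0.5 | 0 | 1.80 | 0.964 |
| +0.5 | -0.2 | 1.08 | 0.86 |
| -0.5 | +0.2 | -1.08 | 0.14 |

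With no effect, the observed direction follows the background. In the last two rows a harmful effect usually looks favourable, and a helpful one usually looks unfavourable.

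**Does a larger group help?** Take four times the sample, n = 52, so sqrt(n) = 7.211. With e = 0 and d = +0.2, Phi(1.44) = 0.93, up from 0.765. With d = 0 it stays at 0.50. More patients make the direction of d + e more certain but do not separate e from d.

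**Does the planned test help?** The Friedman test is an omnibus comparison of three occasions within the same patients. It does not itself state a direction and it has no comparator. In a simulation (n = 13, correlation 0.5 between occasions, the same background shift at Weeks 6 and 12, no SPARKED effect), it rejected at 0.05 in about 5% of replicates with no shift, 14% with a shift of 0.3 SD and 31% with a shift of 0.5 SD. A significant result is therefore not evidence of a SPARKED effect either.

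**The case against.** The strongest reply is that the article already hedges. Section 2.3.7 calls the secondary outcomes exploratory and says that they will not inform a future trial. Section 2.3.9 calls the analysis entirely exploratory. Section 4 declines to derive an effect size, and Section 4.2 disclaims strong conclusions and asks for a randomised trial. The operative text is neutral: Section 2.3.9 compares time points, and Section 3 only tabulates the scores across them. The stated feasibility thresholds concern recruitment and retention. This stands, and it limits the weight of the point. But the hedges concern precision and later use. None withdraws the claim about direction, and the one reason offered is sample size.

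Three stronger readings are tempting, and the documents do not support them.

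- A reader might infer that improvement is likely even if SPARKED does nothing, because patients enter when unwell and regress to the mean. Section 2.3.3 sets no symptom threshold and excludes current suicidal ideation, so entry at a high point is not established. Nor is there a stated reason why adherence or beliefs would drift favourably.
- A reader might infer an ongoing drug response. A current prescription does not imply a recent start, and long-term stable users qualify.
- A reader might infer that treatment changes during the 12 weeks go unrecorded, since Section 2.3.5 describes medication history at baseline only. A journal article commonly leaves visit-level data items to the full protocol, so this cannot be concluded.

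**Conclusion.** The claim about direction is wrong as written. The design can show the direction of within-patient change, but it cannot attribute that change to SPARKED. This rests on the absence of a comparator and not on any assumed size or sign of background change; the probabilities above are illustrations under assumed values. Concurrent antidepressant treatment matters because it is one source of change that cannot be separated from the intervention, whichever way it acts.

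The practical weight is low. The feasibility aims, the sample size of 13 and the progression thresholds are unaffected, and the results are already labelled exploratory. What changes is the conclusion that the trial may state about its secondary outcomes, and the reason given for the limit.

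**What to change.** - In the secondary objective (Introduction) and in Section 4, replace the wording on preliminary effects and on the direction of an effect with: *within-patient change over time, which cannot be attributed to SPARKED*.
- Bring the matching references to impact in Sections 4.1 and 4.3 into line.
- In Section 4.2, add the absent comparator and the concurrent antidepressant treatment as limitations in their own right, and say that a larger single group would not remove them.
- Use the same wording when the results are reported.

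The cost is a few sentences. No design element, visit, measure or sample size changes.

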### 4.1. Strengths

First, this robust multi-method study will adhere to evidence-based frameworks, specifically the MRC framework [38] and the generative co-design framework [39]. The MRC framework has been chosen to guide the study’s design because of its dynamic, iterative approach to developing health interventions, while emphasising the significance of contextual factors in complex interventions [38,74]. Similarly, the generative co-design framework [39] will guide the co-design of SPARKED, thereby enhancing the study’s relevance and potential impact by ensuring it addresses real-world needs and aligns with end-user preferences. By integrating three co-design strategies, this protocol offers a systematic approach to developing a comprehensive family psychoeducational intervention aimed at improving outcomes in MDD. Second, this study harnesses the strengths of both qualitative and quantitative methodologies in developing SPARKED, as well as assessing its feasibility and acceptability. Third, this research is among the first to integrate telehealth psychoeducation for MDD through a structured PPI process, aligning with current priorities in mental health services and nursing research. By focusing on telehealth FPE, this research supports broader efforts to improve access to mental health care. It aligns with the position statement of the International Society of Psychiatric Mental Health Nurses, which recognises telehealth as an effective way to deliver mental health care and advocates for research into its utilisation for mental health services [33]. Fourth, the feasibility study phase explores the impact of the telehealth FPE on clinical and non-clinical patient-related outcomes, providing a balanced focus on outcomes that are often perceived differently by patients, their families, and healthcare providers [75]. Finally, the use of the TIDieR checklist [42] for reporting the details of SPARKED enables replication of the intervention. Although the TIDieR checklist may not fully capture contextual factors that could influence the delivery of a complex intervention [76], adherence to the MRC framework ensures this research remains grounded in identifying and reporting the research context.

### 4.2. Limitations

This protocol has some limitations. The six-week post-intervention follow-up period is relatively short, as the study’s primary aim is to assess the feasibility of the intervention and data collection methods before conducting a larger trial with a longer follow-up. As such, the study will not adequately capture the long-term effects of SPARKED. Next, the feasibility study phase focuses on patient-related outcomes. Evaluating outcomes among family members could have offered an opportunity to ascertain whether SPARKED influences outcomes for both patients and their families. In addition, the small sample size will not permit the evaluation of the intervention’s effect size. Consequently, this study cannot draw strong conclusions regarding the effects of SPARKED. A large-scale RCT of SPARKED will be required to determine the effectiveness of the intervention. Next, the exclusion criteria regarding individuals who are assessed to have imminent suicidal risks limit the generalisability of SPARKED. To improve the generalisability of this research, future studies should consider implementing strategies to optimise contacts with participants for monitoring and assessing suicide risks, as well as establishing a pathway for escalated care. Finally, using telehealth to deliver SPARKED might inadvertently exclude people who lack access to digital devices or digital skills. While this research will report all technical challenges encountered during the study (context-related) to help tailor solutions for future research, future studies should consider providing an easy-to-understand graphic guide on how to use devices or offering in-person support for participants to address this limitation.

### 4.3. Conclusions

This nurse-led study will involve patients with MDD, their family members or significant others, and mental healthcare providers in co-designing telehealth FPE for MDD aimed at improving patient-related outcomes. This research will further assess the feasibility and acceptability of the intervention while examining its preliminary impact on both clinical and non-clinical outcomes. Nurses play a crucial role in mental health care and are uniquely positioned to support patients with MDD throughout their recovery journey. Given that nursing care extends beyond patient care to encompass the support of patients’ family members and social networks, the implementation of FPE by nurses can be effectively embedded within their established professional roles and routine clinical practice. Nursing educational programs and training initiatives should aim to empower nurses to lead innovations that expand nursing care, with the goal of improving patient outcomes and experiences. More importantly, viable policies and strong nursing leadership are essential for creating environments that support evidence-based practices, health innovations, and systemic change in response to the constantly evolving healthcare landscape.

## Figures and Tables

**Figure 1 nursrep-15-00364-f001:**
[figure not shown]
Overall study design informed by the MRC framework [38] and generative co-design framework [39] (p. 5).

**Table 1 nursrep-15-00364-t001:** Key features of the SPARKED protocol.

Element	SPARKED Protocol
Type of intervention	Family psychoeducation
Study participants	Patients with MDD and family members, carers or significant others
Mode of delivery	Telephone or videoconferencing
Format	Single-family
Number of SPARKED sessions	Three
Frequency of sessions	Bi-weekly
Session duration	45–60 min
Intervention duration	Six weeks
Follow-up	At Week 12 (six-week post-intervention)
Outcome measurement timepoints	At baseline, immediately after intervention, and at follow-up

